**CSF biomarkers**		
Aβ (1–42)	≤ 640 pg/ml	Bellomo et al. 2021 [28]
Total-tau	≥ 404 pg/ml	Bellomo et al. 2020 [29]
Phosphorylated Tau 181 (p-Tau)	≥ 56 pg/ml	Bellomo et al. 2020 [29]
Ratio Aβ_1-42/1–40_	≤ 0.068	Doecke et al. 2018 [30], Leitão et al. 2019 [31]
**Ratio** Aβ_1-42 /p-Tau_	≤ 11.8	Leitão et al. 2019 [31]
**EEG**	Classified in physiological vs pathological based on Small World for the seven EEG frequency bands using machine learning technique	Vecchio et al. 2023 [32]
**FDG-PET**	Classified in negative and positive (AD-like, other forms) using the optimised SPM procedure	Della Rosa et al. 2014 [10], Perani et al. 2014 [11]
**APOE- e4**	Classified in none, one allele, both the alleles	

However, these cut-offs were determined to discriminate between normal cognition and AD, but the population under study is at higher risk of developing dementia compared to the normal population. Therefore, for continuous biomarkers the receiver operating characteristic (ROC) curves will be used to identify new optimal cut-offs for the specific population under study. For biomarkers known to be influenced by sex and/or age, the corrected values will be used. In this context, sensitivity and specificity are both considered targets for determining the optimal cut-off; therefore, among all the commonly used methods [33], the distance to the left-upper corner was chosen. This method maximises both sensitivity and specificity and guarantees a better balance between the two measures [34]. Warnings are raised about its use as not always the method leads to an optimal cut-off in the intention of maximising overall correct classification rates compared to the commonly used Youden’s method [35]; therefore, Youden’s method will be also provided for comparison.

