#### Statistical model and variable selection

Initially, an analysis of socio-demographic and clinical variables will be conducted using the Cox model to identify a core of variables significantly associated with the outcome that will be included in the development of the prognostic multivariable model. A check of multicollinearity between predictors will be assessed, then a stepwise selection starting from the full model will be applied using a threshold of 0.10 for removal and 0.05 for re-admission of variables. A final check of variables not selected by stepwise will be conducted using the likelihood ratio test [36, 37]. Age and sex will be forced in the procedure selection and retained in the final model. Subsequently, these selected variables will be included in multivariable models with the addition of individual biomarkers one at a time. The additional predictive value of each biomarker beyond clinical and socio-demographic variables will be calculated. The performance results will be used to determine for each biomarker which form (continuous or categorical) will be chosen for the development of the multivariable prediction model. Categorisation is typically preferred for the application in clinical practice, but as any categorisation implies a loss of information, we will select the biomarker in a categorical form if the loss in performance could be considered negligible with respect to the continuous form. Categorisation will also be chosen in cases where non-linearity is detected for the continuous form. The categorisation according to the threshold provided by the experts (Table 3) will be preferred in case a small loss of performance is observed compared to the continuous form.

The final predictive model will be identified through a multivariable model considering as eligible predictors all the biomarkers and all selected predictors among the clinical and socio-demographic variables using the stepwise selection procedure as described above. Age and sex will be forced into the model selection process. A final check of the result from the automatic selection procedure will be conducted to ensure that no significant biomarkers were excluded and, vice versa, that no negligible biomarkers were included.

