#### Predictive performance

For each biomarker in the categorical form, the accuracy measures (sensitivity, specificity, positive predictive value, negative predictive value, overall accuracy, positive and negative likelihood ratios) will be calculated for comparison with the literature. For continuous biomarkers, the area under the receiver operating characteristic curve (AUC) will be also reported. Moreover, a univariate analysis will be conducted using the proportional hazard Cox model.

To evaluate the performance of the prediction models, several measures will be considered. The concordance c-index with its 95% CI will be provided as a discrimination measure and the extensions of binary AUC to survival analysis proposed by Harrell will be used [40, 41]. The Akaike information criterion will be provided as a measure of the goodness of fit of the model.

The added value on performance of each biomarker to the multivariable model with demographical and clinical variables will be assessed by the category-free Net Reclassification Improvement (NRI), which is the net proportion of events reclassified correctly plus the net proportion of non-events reclassified correctly. The delta AUC (difference in c-statistics) will be also provided [41], and the likelihood ratio test will be used to assess the statistical significance of the incremental contribution of each biomarker [36, 37].

In addition, to assess the predictive performance of the final multivariable model, calibration measures will also be reported [38, 42]. A calibration plot will be done by plotting the observed outcome proportion (on the *y*-axis) versus the ordered predicted outcome probabilities (on the *y*-axis) by quantile of the predicted risk. Subsequently, the calibration intercept and slope and their 95% CI will be estimated. There is a perfect calibration when the intercept is zero and the slope is one. Moreover, overall measures of performance, the Nagelkerke’s *R*^2^ and the Brier score, will be provided. The Brier score is a composite measure of discrimination and calibration with lower scores indicating improved model accuracy, and it will be calculated at a fixed time point (3 years).

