#### Internal validation

The final predictive model will be internally validated using the bootstrap technique with 500 bootstrap samples [38]. The stepwise selection will be repeated in the validation process (i.e. stepwise procedure will be repeated within each bootstrap sample). Consequently, Harrel’s c-index of the predictive model will be adjusted to take into account the estimated potential overfitting and a corrected c-index will be reported. Apparent and corrected calibration measures will be reported [44]. The correction will be performed using the shrinkage factor calculated with bootstrapping. The shrinkage factor may take values between 0 and 1, and a value above 0.90 indicates a small overfitting. As the shrinkage of regression coefficients is an important way to reduce overfitting, the shrinkage factor will be also applied to regression coefficients and intercept of the final model [38] to improve the prediction ability of the regression model when applied to external data. Both the original and shrunken regression coefficients will be reported.

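### The per-biomarker NRI and delta AUC are apparent values with no stated optimism correction; they overstate added value, most of all for ROC-derived cut-offs, and so understate the loss from dichotomising

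*SAP article*

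**What the plan says.** Under Statistical model and variable selection, each biomarker is added singly to the selected clinical and socio-demographic variables: "The additional predictive value of each biomarker beyond clinical and socio-demographic variables will be calculated". The performance results then decide whether a biomarker goes forward in continuous or categorical form. The categorical form is taken if its loss of performance is negligible, with preference for the Table 3 thresholds if the loss is small.

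Under Predictive performance, the added value of "each biomarker to the multivariable model with demographical and clinical variables will be assessed by the category-free Net Reclassification Improvement (NRI", defined as "the net proportion of events reclassified correctly plus the net proportion of non-events reclassified correctly". Two companions follow: "The delta AUC (difference in c-statistics) will be also provided", and "the likelihood ratio test will be used to assess the statistical significance of the incremental contribution of each biomarker".

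Under Statistical analysis method, after Table 3, the plan says that for continuous biomarkers "receiver operating characteristic (ROC) curves will be used to identify new optimal cut-offs for the specific population under study". Among the methods for this, "the distance to the left-upper corner was chosen", and Youden's method is given for comparison.

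Under Internal validation, "The final predictive model will be internally validated using the bootstrap technique with 500 bootstrap samples". The stepwise selection is repeated in each sample, and the c-index, calibration and coefficients are corrected. The one-biomarker models, the NRI, the delta AUC and the cut-off search are not mentioned there.

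**The concern.** The NRI compares each patient's predicted risk with and without the biomarker in the same patients who determined the biomarker's coefficient. The sign of that coefficient follows whatever chance association the sample contains. Events therefore tend to move up and non-events down even if the biomarker carries no information. The category-free version counts every movement, however small, so chance can produce a sizeable value. The delta AUC shares the bias. Searching for a cut-off in the same data adds a second layer of fitting.

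Two things are at stake. The first is the published size of each biomarker's added value, which readers will use to rank biomarkers. The second is the choice of form: if tuned cuts are inflated more than continuous forms, the loss from dichotomising looks smaller than it is.

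**Working it through.** **Planning figures used to set the simulations.** The SAP gives no figure for the behaviour of the NRI. Its Sample size section gives N = 400 evaluable, 27 to 40% incidence and 20% dropout, and these reproduce:
- Table 2, sensitivity 80% at 27% incidence: 1.96 × √(0.8 × 0.2 / (400 × 0.27)) = 7.5%. Specificity 80% at 40% incidence: 1.96 × √(0.8 × 0.2 / (400 × 0.60)) = 5.1%. All 18 entries agree to one decimal.
- 400 / (1 − 0.20) = 500.
- Events per parameter, with a shrinkage target of 0.9 (assumed) and R² = 0.31: 1 / ((0.9 − 1) × ln(1 − 0.31/0.9)) = 23.7 patients; × 0.16 × 2.5 = 9.5 events.

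**Measure.** NRI = [P(up | event) − P(down | event)] + [P(down | non-event) − P(up | non-event)], computed in the development sample.

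**Useless biomarker.** Logistic and Cox simulations, N = 350 to 400, 3 to 8 clinical covariates, about 23 to 41% events. The Cox runs had 6-monthly visits, 15% dropout and a Kaplan–Meier-based NRI at 3 years. The biomarker was independent of the covariates. Covariate effects are assumptions (logistic baseline AUC 0.71 to 0.80). Delta AUC is from the logistic runs.

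| Form | NRI > 0 | Mean NRI | Delta AUC > 0 | LRT rejects at 5% |
|---|---|---|---|---|
| Continuous | 76–83% | 0.07–0.09 | 74–76% | 5–7% |
| Fixed cut | 79–87% | 0.07–0.08 | – | 5–7% |
| Upper-left corner cut | 91–97% | 0.13–0.16 | 86–89% | 13–20% |
| Youden cut | 96–100% | 0.16–0.20 | 94–96% | 26–38% |

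At N = 400 and about 40% events the mean NRI is about 0.07 (continuous), 0.13 (corner) and 0.17 (Youden).

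**Informative biomarker with a truly linear effect.** Cox, N = 400, about 41% events, 2,000 runs. Mean apparent NRI, with the difference from the continuous form in brackets:

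| HR per SD | Continuous | Fixed cut at 0.3 SD | Corner | Youden |
|---|---|---|---|---|
| 1.25 | 0.235 | 0.186 (−0.049) | 0.255 (+0.020) | 0.282 (+0.047) |
| 1.50 | 0.412 | 0.326 (−0.086) | 0.397 (−0.015) | 0.417 (+0.005) |
| 2.00 | 0.660 | 0.537 (−0.123) | 0.608 (−0.052) | 0.620 (−0.040) |

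Here dichotomising always discards information, and the fixed cut shows this. The corner cut turns the loss into an apparent gain at HR 1.25 and nearly hides it at HR 1.50. The position of the fixed cut explains little of the gap. The correlation of a standard normal variable with its indicator above c is φ(c)/√(Φ(c)(1 − Φ(c))), which is 0.798 at c = 0 and 0.785 at c = 0.3.

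**Overlap with noise, continuous form.** The null 95th percentile of the NRI is 0.22. At HR 1.25 the 5th to 95th percentiles are 0.05 to 0.42. At HR 1.5 the 5th percentile is 0.23, and at HR 2 it is 0.49. LRT power is 81%, 99.9% and 100%.

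**The case against.** A reader might infer that the plan judges added value by the NRI alone and that the NRI cannot tell an informative biomarker from noise. The documents and the figures do not support that:
- The same paragraph gives the delta AUC and assigns statistical significance to the likelihood ratio test, which holds about its level for continuous and pre-specified forms.
- No rule treats a positive NRI as evidence, so the frequencies above show bias and are not the error rate of a stated decision.
- The size of the NRI separates markers of HR 1.5 per SD or more from noise almost fully when they are continuous.
- All biomarkers are eligible for the final model, entry is by stepwise p-values, and that model does receive a bootstrap correction.

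The ROC-cut figures also have limited reach. EEG, FDG-PET and APOE need no ROC cut, Table 3 thresholds are preferred if the loss is small, and Youden is only a comparison. The form-choice text refers to performance results without naming the NRI, and the mean null gain in c-statistic is only 0.001 to 0.004.

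The settings matter too. With a useless biomarker correlated 0.4 with a clinical covariate, the NRI is positive in 81% (continuous), 82% (corner) and 94% (Youden) of runs. The ROC-cut null figures also depend on the direction of abnormality being read from the data. A repeat with the direction fixed beforehand, natural for markers listed in Table 3, brought the corner cut close to the continuous form, while Youden stayed clearly inflated. For the HR 1.25 marker, fixing the direction made practically no difference, so the form comparison is not affected.

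What stands is that the effect sizes are uncorrected, that the likelihood ratio test supplies no corrected size, and that this test is least reliable for the forms most inflated.

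**Conclusion.** The point holds as one about uncorrected optimism. The planned per-biomarker NRI and delta AUC are apparent values. Under the assumed settings a useless, independent biomarker yields a positive NRI in about 76 to 83% of runs when continuous and 91 to 100% when cut at a ROC-derived value with its direction taken from the data. A positive value is therefore not evidence of added value, and markers near HR 1.25 per SD overlap with noise.

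The likelihood ratio test is an adequate safeguard for continuous and Table 3 forms but not for ROC-derived cuts. Because tuned cuts gain more from the bias than continuous forms, the comparison of forms understates the cost of dichotomising, most clearly for weak markers. How often the plan's own rule would choose the wrong form has not been simulated. The exact frequencies rest on assumed covariate effects and correlations; the upward bias itself follows from evaluating the models in their own fitting data.

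**What to change.** Extend the Internal validation section to the one-biomarker models. Apply the 500 bootstrap samples to each biomarker in each candidate form, refit the models with and without the biomarker, and repeat the ROC cut-off search in every sample. Under Predictive performance, report the optimism-corrected difference in c-index, and in 3-year Brier score, as the added value. State under Statistical model and variable selection that these corrected values decide the form. If the NRI is wanted for comparison with the literature, keep it as descriptive and bootstrap-corrected, and do not use it to choose the form. State that the nominal likelihood ratio p-value is not relied on for ROC-derived cuts.

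The cost is SAP wording and modest computing, somewhat more than one loop per biomarker because several forms are compared. No new data are needed. The added-value figures will be smaller.

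### The likelihood ratio test of a biomarker's added value does not exclude categories whose cut-off was tuned on the same outcomes; if such a category is tested, the 5% error rate becomes roughly 8-10%, and up to about 15-18%

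*SAP article*

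**What the plan says.** Four statements in the SAP article bear on this point.

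- **Cut-off search.** After Table 3, the plan notes that the published thresholds were set to separate normal cognition from AD. It therefore plans that "for continuous biomarkers the receiver operating characteristic (ROC) curves will be used to identify new optimal cut-offs for the specific population under study". As criterion, "the distance to the left-upper corner was chosen"; of Youden's index it says that the "method will be also provided for comparison".
- **Choice of form.** Under Statistical model and variable selection, each biomarker is added singly to the clinical model, and "The performance results will be used to determine for each biomarker which form (continuous or categorical) will be chosen". The rule is that "we will select the biomarker in a categorical form if the loss in performance could be considered negligible with respect to the continuous form". Non-linearity also leads to categorisation. A priority follows: "The categorisation according to the threshold provided by the experts (Table 3) will be preferred in case a small loss of performance is observed". Neither a negligible nor a small loss is given a number.
- **Test.** Under Predictive performance, "the likelihood ratio test will be used to assess the statistical significance of the incremental contribution of each biomarker". The form tested, the reference distribution and the significance level are not given for this test. The 5% level appears under Baseline characteristics, for the comparison of converters with non-converters.
- **Bootstrap.** Under Internal validation, the stepwise selection is repeated in each of 500 samples, and the c-index, calibration and coefficients are corrected. The cut-off search is not named among the repeated steps.

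**The concern.** The chi-square reference for a likelihood ratio test holds for a covariate defined without sight of the outcome. A ROC-derived category is defined by the outcome: its boundary lies where converters and non-converters in this cohort separate best. Testing that split on the same participants counts the chance separation found by the search as evidence, so the p-value is too small.

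The exposure is uneven. Eleven continuous measures can receive a searched cut-off: MMSE, DFR, five CSF measures, and right and left hippocampal volume by two techniques (1 + 1 + 5 + 4 = 11). FDG-PET, EEG and APOE enter in classes that do not come from a ROC search in this cohort. In a study meant to identify which biomarkers predict conversion, some would be judged at a true 5% and others at a higher rate without the reader knowing.

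**Working it through.** **Inputs from the SAP article.** 400 evaluated participants; 40% conversion at 3 years, with 27% as the low end of Table 2; corner criterion chosen, Youden for comparison. The plan gives no error rate for this test, so there is none to reproduce. Its sample-size figures do reproduce. For example, the Table 2 half-width for 80% sensitivity at 27% incidence is 1.96 × √(0.8 × 0.2 / (400 × 0.27)) = 7.5%, and 400 / 0.8 = 500.

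**Assumptions, because the plan gives no value.** 5% level; chi-square reference with 1 degree of freedom (critical value 3.841); four prognostic clinical covariates with log hazard ratios 0.5, 0.4, 0.3 and 0.3; exponential event times with censoring only at 3 years; a normally distributed biomarker with no effect.

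**Steps in each simulated study** (3,000-4,000 studies per setting)

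1. Choose the cut-off c on 3-year status. The corner method minimises √[(1 − Se(c))² + (1 − Sp(c))²]; Youden maximises Se(c) + Sp(c) − 1.
2. Fit the Cox model with the clinical covariates Z, then with Z and the category.
3. Compute LR = 2 × [ℓ(Z, category) − ℓ(Z)] and reject if LR > 3.841.

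Direction is either fixed beforehand or taken from whether the observed AUC lies above or below 0.5. The second option gives the search a second chance to find a separation.

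**False-positive rates, N = 400, 27-40% conversion**

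| Form tested | Direction fixed | Direction from data |
|---|---|---|
| Corner cut-off, adjusted model | 7.9-8.9% | 14.7-16.3% |
| Youden cut-off, adjusted model | 18.8-21.1% | 29.8-34.0% |

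Across all settings, adjusted or not, the continuous form gave 4.3-5.9% and a cut-off fixed outside the data gave 4.4-6.3%.

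Monte Carlo error is small beside these gaps. At 8.5% with 3,000 studies it is 1.96 × √(0.085 × 0.915 / 3000) = 1.0 percentage point.

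**Robustness**

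- Further runs of the corner method gave 9.2% and about 10% with direction fixed, and 15.5% and 17-18% with direction from the data. The working ranges are therefore roughly 8-10% and 15-18%.
- If the null marker correlates 0.4 with a clinical covariate, the corner rate is about 7-10%; one pair of runs gave 8.9% with direction fixed and 9.7% with direction from the data.
- Youden ranged over about 13-38% across these settings.
- The Discussion says the recruitment target was missed. With 300 participants, 30% conversion and direction from the data, the rates were 5.0% (continuous), 15.6% (corner) and 32.5% (Youden), so a smaller sample does not change the picture.
- The plan's order of preference was also imitated: published cut-off, then ROC cut-off, then continuous form, with an assumed tolerated c-index loss of 0 to 0.02. At 400 participants and 40% conversion this gave 5.7-11.2% with direction fixed and 5.3-13.5% with direction from the data.

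**The case against.** The strongest reply is that the plan need not reach the inflated test. It keeps the continuous form unless the loss from categorising is negligible or non-linearity appears, and it prefers the Table 3 threshold when the loss is small. Both of those forms hold about 5%. This stands as a limit on the claim: the higher rates apply only when the ROC-derived category is the form tested, and under the plan's order of preference the rate can be close to nominal. It does not remove the point, because the tolerance is not quantified and nothing excludes the ROC-derived category from the test.

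Four stronger readings are tempting, and the document does not support them.

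- **A reader might infer that a third of useless biomarkers would be declared significant.** That is the Youden rate with data-chosen direction. The plan chose the corner method and shows Youden for comparison only.
- **A reader might infer that about 15% is the general rate.** It requires direction to be taken from the data and a marker independent of the covariates. Table 3 gives a direction of abnormality for MMSE, DFR, hippocampal volume and the CSF measures. Several markers are also age-related and age is forced into the model; correlation with a covariate lowers the rate.
- **A reader might infer that this test decides which biomarkers enter the final model.** All biomarkers are eligible for it. The test accompanies NRI and the difference in c-statistics as evidence of added value.
- **A reader might infer that shuffling the raw biomarker values, with the search repeated, is an exact cure.** Shuffling also breaks the marker's relation to the clinical covariates, so it tests full independence rather than no added value. Applying the independent-marker critical value to null markers correlated 0.4, as an approximation to that shuffle, gave 3.6% (corner) and 2.7% (Youden), which is conservative.

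**Conclusion.** The point holds in conditional form and should be fixed. As written, the plan allows the added value of a continuous biomarker to be tested on a category tuned to the same outcomes, with no correction. In that case the corner method gives roughly 8-10% false positives with direction fixed beforehand, and up to about 15-18% with direction from the data and a marker independent of the covariates, against a nominal 5%. Internal validation as described adjusts the performance measures and coefficients of the final model and leaves these p-values untouched.

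The size depends on the assumed 5% level, chi-square reference, covariate effects and marker distribution. The direction of the error does not depend on those exact values: searched categories exceeded 5% in every setting in which they were the form tested.

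**What to change.** Under Predictive performance, state that the likelihood ratio test of added value for a continuous biomarker uses its continuous form, with a pre-specified non-linear term if needed, or the pre-set Table 3 category. State also that no ordinary chi-square p-value is reported for a ROC-derived category. Name the significance level and the form tested for each biomarker.

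For MMSE the continuous form is the practical choice. The Table 3 category is a corrected score below 24, while inclusion requires a corrected score of at least 24. The two corrections are described differently (age and sex; age and education), so the category may not be quite empty, but few participants are likely to fall in it.

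If a p-value for a ROC-derived category is still wanted, take it from a resampling null that repeats the cut-off search and keeps the biomarker's relation to the clinical covariates, for example by permuting the biomarker's residuals given those covariates. That variant was not simulated here and should be checked before use.

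The cost is a few sentences of wording and, only if the last option is taken, a short computation. No new data are needed. Some p-values may become less favourable.
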